## 1 Abstract

2 Subthreshold depression is a substantial risk factor for the development of major depression. It is  
3 associated with poorer health, functional disabilities, and reduced quality of life in older adults. There is a  
4 paucity of cost-effective psychosocial interventions for this population in primary care worldwide,  
5 particularly in low- and middle-income countries. We present a protocol for evaluating the effectiveness and  
6 cost-effectiveness of the Viva Vida programme, a 6-week self-help digital psychosocial intervention for  
7 treating older adults with subthreshold depressive symptoms in primary care with a two-arm, individually  
8 randomised controlled trial with a 1:1 allocation ratio with integrated economic and process evaluations. We  
9 will include 450 individuals 60 years and older with subthreshold depressive symptoms (score between five  
10 and below 10 on the 9-item Patient Health Questionnaire (PHQ-9)), registered with one of the 46 primary  
11 care clinics in Guarulhos, Brazil. The Viva Vida programme will be delivered via automated audio and visual  
12 WhatsApp messages, with psychoeducation and behavioural activation contents. It involves 48 messages,  
13 delivered twice-daily, four days a week. Participants in the control arm will receive a single message with  
14 general information about depression. The primary outcome is the depressive symptoms at the three-month  
15 follow-up as measured by PHQ-9, which will be compared between study arms. The cost-effectiveness of the  
16 intervention will be assessed at five months. A detailed process evaluation will explore context and  
17 implementation outcomes. The Viva Vida programme is an innovative digital psychosocial intervention  
18 delivered via WhatsApp messaging without the participation of health professionals. The evaluation of the  
19 Viva Vida programme will contribute to the development of simple and cost-effective models of remote self-  
20 help interventions for reducing depressive symptoms among older adults with subthreshold depression in  
21 primary care. The protocol is registered with Registro Brasileiro de Ensaios Clinicos (ReBEC) (RBR-6c7ghfd).

## 22 Introduction

23 The development of simple and effective treatments for older adults with subthreshold depression is an  
24 important public health issue and has been identified as a neglected area of research [1–3]. The definition  
25 and diagnostic criteria of subthreshold depression (also known as subsyndromal depression, subclinical

26 depression or minor depression) are heterogeneous [1]. Broadly speaking, subthreshold depression requires  
27 the presence of at least one core symptom of depression (depressed mood or anhedonia), while the severity  
28 of symptoms does not meet the criteria for a diagnosis of depression [4,5].

29 The negative impact of subthreshold depression on the health of older people and healthcare systems  
30 is well known. Subthreshold depression is associated with functional disability, reduced quality of life,  
31 loneliness, suicide attempts, mortality and increased healthcare utilisation [1,6–8]. Furthermore, the high  
32 prevalence of subthreshold depression among older adults in the community, the persistence of symptoms  
33 over time, and the progression to moderate and severe forms of depression in many cases highlight the  
34 public health challenge of addressing this condition [3].

35 A review of trials conducted in the 2000s to reduce depressive symptoms in older, community-dwelling  
36 adults with subthreshold depression recommended the use of psychotherapy [9]. This review showed that  
37 psychotherapeutic approaches (i.e. cognitive behavioural therapy, problem solving therapy, physical  
38 activation and behavioural activation) were safe and effective in reducing depressive symptoms in primary  
39 care settings [10–13]. However, only one study in this review evaluated the effectiveness of a remote  
40 intervention method using a web-based self-administered cognitive behavioural therapy [11]. More recently,  
41 the UK Casper trial provided evidence of the effectiveness of a collaborative care programme, delivered  
42 mainly remotely, in reducing depressive symptoms and progression to moderate and severe symptoms in  
43 older adults with subthreshold depression in primary care [14]. The Casper programme has innovative  
44 components. Nursing assistants delivered a rapid and relatively inexpensive behavioural activation  
45 programme over the telephone, improving access to treatment.

46 The availability of remote mental health interventions has recently increased [15], driven by the COVID-  
47 19 pandemic. A recent umbrella review of 38 systematic reviews showed that the restrictions on social  
48 contact between people imposed by COVID-19 measures have impacted how mental health services are  
49 provided. Synchronous tools (e.g. video conferencing) and, to a lesser extent, asynchronous tools (e.g. mobile  
50 applications) have been used to provide remote mental health care to patients, particularly in high-income  
51 countries [16]. However, the scarcity of evidence of research in primary care settings worldwide does not

allow us to determine which forms of synchronous or asynchronous self-help telepsychosocial approaches are effective for older adults with subthreshold depression. Identifying cost-effective psychosocial treatments and the older adults who are most likely to benefit from them is urgent in low- and middle-income countries (LMICs), where primary care is struggling to meet the physical and mental health needs of a rapidly growing older population.

We will conduct a randomised controlled trial to evaluate the effectiveness and cost-effectiveness of the Viva Vida programme (PRODIGITAL), a 6-week digital psychosocial intervention delivered via automated audio and visual WhatsApp messages for the treatment of older adults with subthreshold depressive symptoms in primary care in Guarulhos, Brazil. A process evaluation using qualitative methodology will examine the implementation outcomes (acceptability, appropriateness, fidelity, and feasibility) of the intervention, the contextual barriers and facilitators to implementing this programme.

## Methods

We present the protocol of a two-arm (1:1 allocation ratio) randomised controlled trial (RCT) with integrated economic and process evaluations.

## Study setting

The study will recruit individuals registered at 46 primary care clinics in underprivileged areas of Guarulhos, known as Unidades Básicas de Saúde (UBSs). All primary care clinics have Family Health Teams (FHTs) and care is based on the Family Health Strategy model. Guarulhos has a population of approximately 1.4 million. The average per capita household income is BRL 791 reais (approximately USD 159 dollars in 2023) [17]. In Guarulhos, 13.8% of the population is 60 years or older, of which 55.7% are women [18], and 14.6% are illiterate [19]. In the Southeast region of Brazil, where Guarulhos is located, 75.7% of older adults have a mobile phone [20] and 64.9% have connected to the Internet in the last three months [21].

## 74 **Participants**

### 75 **Inclusion criteria**

- 76 (a) Individuals aged 60 years or over registered with one of the 46 participating UBSs;
- 77 (b) Individuals able to receive and listen to WhatsApp messages;
- 78 (c) Individuals screening positive for subthreshold depressive symptoms assessed with the 9-item Patient
- 79 Health Questionnaire (PHQ-9), defined as a score of at least 1 on the PHQ-2, which includes the first two
- 80 questions of the PHQ-9 (depressed mood and anhedonia), and a PHQ-9 total score of at least five and less
- 81 than 10 [4,22,23].

### 82 **Exclusion criteria**

- 83 (a) Individuals with communication problems (e.g., non-Portuguese speaking or cognitive impairment to
- 84 the extent that these interfere with study assessments or to participate in the intervention);
- 85 (b) Individuals with visual or hearing impairments to the extent that they interfere with study assessments
- 86 or to participate in the intervention;
- 87 (c) Individuals who are unable to participate in the study for five months;
- 88 (d) Individuals identified as being at acute suicide risk (i.e. a suicide attempt in the two weeks before the
- 89 screening assessment) using the Immediate Suicide Risk Protocol [24];
- 90 (e) Individuals living in the same household as another study participant;
- 91 (f) Individuals who participated in the PROACTIVE trial [25].

## 92 **Interventions**

93 Participants in the intervention arm will receive a self-help digital psychosocial intervention delivered

94 via audio and visual WhatsApp messages. The control arm will receive a single audio message. The research

95 team will not interfere with the health care that participants may receive during and after their participation

96 in the trial.

## 97    **Digital psychosocial intervention**

98            The Viva Vida programme was adapted from the short, animated videos shown by community health  
 99 workers to older adults with depressive symptomatology in the RCT testing the PROACTIVE intervention  
 100 [24,25] and grounded in the theories of psychoeducation [26] and behavioural activation [27]. Behavioural  
 101 activation is an approach in mental healthcare that aims to promote behaviours that activate positive  
 102 emotions, as well as avoid those that worsen depressive symptoms, and integrate them into one's routine  
 103 [27]. The programme consists of 48 messages that will be sent to participants via WhatsApp over six weeks,  
 104 four days per week. Each day, they will receive one message in the morning and one in the afternoon. No  
 105 support of health professionals will be provided as part of the intervention.

106            There are two types of messages: audio messages and images with short texts. Audio messages last, on  
 107 average, three minutes and are based on the storytelling technique, a communication tool that can attract  
 108 attention, arouse emotions and engage listeners to influence their attitudes and beliefs [28]. We chose audio  
 109 messages because of the low level of education and income of the older adults living in disadvantaged areas  
 110 of Guarulhos. The audio messages are short to make Viva Vida viable for older people with mobile phones  
 111 with low storage capacity. Through the audio messages, two fictitious characters ([name] and [name])  
 112 share experiences as if they had participated in the Viva Vida programme. These characters share what they  
 113 have learned about depression (psychoeducation), how they have felt, and what kind of pleasant and  
 114 meaningful activities they have done, and the ones they have avoided to increase positive interactions with  
 115 people and the environment (behavioural activation). The messages also include health promotion tips, such  
 116 as information on diet, physical activity, the importance of other health treatments, and relapse prevention.  
 117 The audio and visual messages advise participants to contact health services if they feel that their depressive  
 118 symptoms are not improving or are getting worse. The characters use language, vocabulary, tone and manner  
 119 appropriate to the target audience. They are realistic to create empathy for the study participants when  
 120 listening to the messages. The content of the Viva Vida programme follows with the WHO recommendations  
 121 for digital interventions for depression [29] and the theoretical basis of interactive health communication

122 applications [30,31]. It also follows guidelines suggesting that patients should be educated about depression  
 123 and encouraged to self-manage their symptoms [32,33].

124 To show how behavioural activation technique is embedded into the Viva Vida programme, we present  
 125 an example of one of the audio messages in which [name] practises what she has learned during the Viva  
 126 Vida programme. She shares with the listener her experience of doing an activity she enjoys has helped to  
 127 improve her mood.

128 *([name], message 11, week 2) "I want to tell you something that happened to me the other day.*  
 129 *I woke up upset, feeling down, and I thought to myself I have to get up and do something. I have a little*  
 130 *garden here at home and I love to plant and take care of the plants. At first, I felt discouraged, but there*  
 131 *I was, watering the lettuce, and working the soil. You know, after a while I got so distracted that I didn't*  
 132 *even realise I was feeling discouraged. It was really cool. That was when I realised that doing something*  
 133 *we like, something we care about, changes our mood. It works. And if it works for me, it will work for you*  
 134 *too. Give it a try!"*

135 As part of the programme, participants will receive one extra message at the end of each week, using  
 136 the WhatsApp quick reply tool, with questions about their experience of participating in Viva Vida. These  
 137 questions will investigate whether the messages helped them understand the signs of depression, if they  
 138 could choose and do activities that may help them feel better, whether the Viva Vida programme is helping  
 139 them to feel better, and whether they liked being part of the programme. The WhatsApp quick reply tool  
 140 allows participants to answer the question by selecting one pre-defined answer, for example, *yes, more or*  
 141 *less, or no*. After replying, participants will receive an automated pre-recorded audio response. These  
 142 messages will also invite participants to share further comments about the programme by sending  
 143 spontaneous WhatsApp messages.

## 144 **Single message**

145 Participants allocated to the control arm will receive a single audio message of approximately six  
 146 minutes via WhatsApp. This message informs them about the main signs of depression, simple ways to

147 improve their mood, and advises them to contact health professionals for further support if they do not feel  
148 better or need additional care.

## 149 **System to deliver the messages**

150 The technical research team will coordinate the delivery of the messages. We will use a web system  
151 integrated with the WhatsApp Business Application Programming Interface (API), which is managed by an  
152 intermediary company. This system is hosted on a cloud service where access is restricted by both  
153 authentication and authorisation processes. Data flowing to and from browsers is also protected through the  
154 use of encryption. The WhatsApp Business API allows the research team to capture the date and time  
155 (timestamp) when messages are sent, delivered and opened, replies to the quick reply tool, and the content  
156 of spontaneous messages. The API enables customised messages (e.g. messages with the recipient's name)  
157 and the attachment of audio and image files. Messages will be scheduled weekly and delivered using a job  
158 scheduler on the server.

159 During the first two weeks of the programme, a member of the technical support team (who does not  
160 take part in the other activities of the study) will contact participants who are not receiving or opening the  
161 messages to check if they are experiencing any technical problem. We will identify these participants through  
162 the Viva Vida web dashboard, which will show the status of messages as *sent to intermediary company*  
163 *platform, sent to participant, delivered to participant, or opened by the participant*. During the remaining  
164 four weeks of the Viva Vida programme, participants will be able to contact the technical support team if  
165 they are not receiving the messages.

166 We will remove participants who block their mobile phones from receiving the Viva Vida messages to  
167 comply with the WhatsApp policy and keep our system functional. These participants will not receive new  
168 intervention messages, but will be contacted again during follow-up evaluations unless they contact us to  
169 withdraw their consent to participate in the study.

## 170 Outcomes

171 Follow-up assessments will take place three and five months after sending the first message  
172 (intervention arm) or the single message (control arm).

### 173 Primary outcome

174 The primary outcome will be the (continuous) PHQ-9 score as a measure of depressive symptoms at the  
175 three-month follow-up, which will be compared between study arms as allocated.

### 176 Secondary outcomes

177 Depressive symptoms(mean PHQ-9 score) at five months. Other secondary measures assessed at three  
178 and five months will be the proportion of participants with clinically significant depressive symptomatology  
179 (PHQ-9 $\geq$ 10), change in anxiety symptomatology as measured by the 7-item Generalised Anxiety Disorder  
180 (GAD-7) [34], loneliness as measured by the 3-item University of California, Los Angeles (UCLA) Loneliness  
181 scale (3-item UCLA) [35], quality of life measured by the European Quality of Life five-dimensional  
182 questionnaire, five-level version (EQ-5D-5L) [36], and capability well-being measured by the ICEpop  
183 CAPability measure for Older people (ICECAP-O) [37]. The cost-effectiveness of the Viva Vida programme will  
184 be assessed at the five-month follow-up.

## 185 Sample size

186 To detect what we consider to be a relevant clinical difference between the two randomised arms of  
187 0.33 standard deviations [14], 142 to 162 individuals in each arm gives 80% to 85% power at a two-sided 5%  
188 significance level. Data from our PROACTIVE pilot study [38] (PHQ-9 means of 5.9 and 6.4 with a standard  
189 deviation of 1.5; data not published) suggest that this effect size is feasible for this kind of intervention. We  
190 anticipate 25% attrition and therefore plan to recruit 225 individuals in each arm, for a total sample size of  
191 450.

## 192 Recruitment

193 The Guarulhos Health Secretariat will provide a list with contact details of all individuals aged 59 years  
 194 or older who are registered in the participating UBSs (the slightly lower age limit compared to the relevant  
 195 inclusion criterion is so that we include individuals who would be 60 years old during the recruitment period).  
 196 Names duplicated on the list, individuals without a mobile phone number, and participants from our previous  
 197 RCT conducted in Guarulhos [24] will be excluded. The remaining individuals (alphabetical ordered) on the  
 198 list will receive a random ID number. The recruitment will follow the ID number in ascending order. This new  
 199 list will be used to simultaneously recruit participants for two RCTs evaluating a digital intervention for older  
 200 adults with depressive symptoms being conducted by our research group [39]. These two studies will use the  
 201 same protocol to recruit participants; only the inclusion criterion for the severity of depressive symptoms  
 202 will be different. In the present study, we will recruit older adults with subthreshold symptoms of depression  
 203 as defined above.

204 The research team will contact via WhatsApp message individuals who have at least one mobile phone  
 205 number. This message will briefly describe the study and inform these individuals that a research assistant  
 206 will contact them by phone. Only those whose WhatsApp message is successfully delivered (i.e. an active  
 207 WhatsApp number) will be contacted by phone and invited to start the recruitment interview. This interview  
 208 will consist of three stages:

- 209 (a) Screening assessment: will assess inclusion criteria (age, WhatsApp use and assessment of depressive  
 210 symptoms) and exclusion criteria (communication and engagement problems, acute suicide risk, and health  
 211 conditions that prevent participation in the trial);
- 212 (b) Baseline assessment: participants screened positive for subthreshold depressive symptoms and with no  
 213 exclusion criteria will be assessed for anxiety, loneliness, quality of life, capability well-being, socioeconomic  
 214 profile (marital status, race, education level, living arrangement, and personal and household income), and  
 215 alcohol and tobacco use;
- 216 (c) Invitation to participate in the study.

Whenever possible, the screening and baseline assessments will be carried out consecutively during the same telephone call. Eligible participants will then be invited to participate in the study. If the participant is unable to complete all three stages of the interview in the same phone call, the research assistants will arrange another time to complete recruitment no more than 28 days after the PHQ-9 screening. Before screening and inviting individuals to participate in the study, we will inform them about the study and obtain their consent. The full study timeline is shown in Fig 1, and a detailed diagram of the study procedures is shown in Fig 2.

**Fig 1. SPIRIT schedule of enrolment, interventions and assessments.** 3-item UCLA, 3-item University of California, Los Angeles (UCLA) Loneliness scale; EQ-5D-5L, European Quality of Life five-dimensional questionnaire, five-level version; GAD-7, 7-item Generalised Anxiety Disorder; ICECAP-O, ICEpop CAPability measure for Older people; PHQ-9, 9-item Patient Health Questionnaire. The qualitative interview will be conducted with 24 purposely selected participants from the intervention arm.

**Fig 2. Diagram of the main procedures of the trial.** Trained research assistants will contact individuals registered in 46 UBSs from Guarulhos, São Paulo, Brazil. After a three-step recruitment interview, participants will be allocated (1:1) to control (one audio message) or intervention (Viva Vida programme) arms. A web system will send messages to both arms, and a web dashboard will identify technical problems. Follow-up assessments at three and five months will be conducted. Qualitative assessments will be made in selected participants between follow-up assessments. Quality control will be performed in a sample of baseline and follow-up assessments. API, Application Programming Interface; UBS, primary care clinics known as Unidades Básicas de Saúde.

## Blinding

Given the differences in the number and content of the messages received by the intervention and control groups, blinding of participants will not be feasible. The team of researchers responsible for recruitment and follow-up assessments and the team responsible for the intervention will work independently. Research assistants conducting recruitment and follow-up assessments will be blinded to group allocation. Whenever possible, the same research assistant will not conduct more than one interview (recruitment or follow-up) with the same participant. The risk of contamination is therefore very low. Messages sent to participants in both arms of the study will be delivered remotely, and participants will not be informed about other people enrolled in the RCT.

## Data collection and management

Data will be collected and managed using the REDCap software, hosted at the Hospital das Clínicas da Faculdade de Medicina da Universidade de Sao Paulo [40,41]. REDCap is a secure, web-based software platform designed to support data capture for research studies, providing: 1) an intuitive interface for validated data capture; 2) audit trails for tracking data manipulation and export procedures; 3) automated export procedures for seamless data downloads to standard statistical packages; and 4) procedures for data integration and interoperability with external sources. Recruitment and follow-up will be conducted by telephone by independent research assistants. Research assistants will be trained in the correct use of research questionnaires and data entry into the REDCap software. They will obtain permission from

266 participants to record the interviews. The recorded interviews will be used to assess the quality of data  
267 collection.

268 Assessments of depressive symptomatology (PHQ-9), anxiety symptomatology (GAD-7), loneliness (3-  
269 item UCLA), health-related quality of life (EQ-5D-5L), capability well-being (ICECAP-O), alcohol and tobacco  
270 use will be administered at recruitment and repeated at three- and five-month follow-up. We will also ask  
271 participants if they need help with activities of daily living, recent time lost from work, consultations with  
272 health professionals (including mental health professionals), hospital admissions, and ongoing treatment for  
273 depression during the follow-up period. Severe adverse events associated with trial participation, such as  
274 suicide attempts, hospitalisation and death will be assessed for all participants in both follow-up  
275 assessments. At the end of both follow-up assessments, participants allocated to the intervention arm will  
276 be asked about their experience with the Viva Vida programme. We will collect data from the electronic  
277 health system's records on psychotropic medication use and consultations with general practitioners and  
278 nurses for all participants during the five months they were enrolled in the RCT. This will be done shortly  
279 after the end of the last follow-up.

280 An independent researcher, who will not conduct interviews with participants, will carry out quality  
281 control of the recruitment and follow-up assessments. A sample of the recorded interviews will be reviewed  
282 to ensure adherence to the script and the quality of data collected.

283 We will leave a 4-week window for the follow-up assessments to minimise attrition. The three-month  
284 follow-up will take place between the 12th and 16th week, and the five-month follow-up between the 20th and  
285 24th week after sending the first message (intervention arm) or the single messages (control arm). If the  
286 research assistants have difficulty contacting participants by phone during the follow-up window, then they  
287 will send an audio and/or a text message via WhatsApp to try to remind participants of the interview. If there  
288 is no response, the UBSs managers will be contacted to assist in reaching the participant. As a last resort,  
289 after three weeks of unanswered contact attempts, a research assistant will visit the participant at home to  
290 conduct a face-to-face assessment.

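### Severe adverse events are defined by association with the trial and captured, as far as the protocol states, only at the two follow-up assessments, so deaths, hospitalisations and suicide attempts are likely to be undercounted

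*Protocol*

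**What the plan says.** All the relevant text is in the protocol; the statistical analysis plan was not available for this review.

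- Data collection and management opens the safety sentence with "Severe adverse events associated with trial participation, such as" and continues that "suicide attempts, hospitalisation and death will be assessed for all participants in both follow-up" assessments. Those assessments are telephone interviews at three and five months, with a home visit as a last resort.
- The preceding sentence of that section has participants asked about consultations with "health professionals (including mental health professionals), hospital admissions, and ongoing treatment for" depression during follow-up. This question carries no condition about association with the trial.
- The same section plans an extraction from the electronic "health system's records on psychotropic medication use and consultations with general practitioners and" "nurses for all participants during the five months they were enrolled in the RCT". Deaths, admissions and suicide attempts are not among the listed items.
- For people who cannot be reached, the section says that if there "is no response, the UBSs managers will be contacted to assist in reaching the participant", and that "after three weeks of unanswered contact attempts, a research assistant will visit the participant at home to" carry out the assessment there.
- Sample size states that the investigators "anticipate 25% attrition and therefore plan to recruit 225 individuals in each arm, for a total sample size of" 450.
- Blinding keeps the follow-up research assistants unaware of allocation.
- Statistical methods describes no comparison of harms between arms.

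**The concern.** Two features of the collection rule work against a complete count.

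The first is the definition. Read literally, an unrelated death or suicide attempt need not be recorded as a severe adverse event. Read loosely, the qualifier does nothing. The protocol names no one to judge association and gives no criterion, so two research assistants could treat the same event differently.

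The second is the occasion. A person who has died or is in hospital is among those least likely to complete a telephone assessment. If that assessment is the only stated point of capture, events are most easily missed in the people most likely to have had one.

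What is at stake is how the trial's harms can be read. In people aged 60 and over with depressive symptoms, a low event count is reassuring only if ascertainment is close to complete.

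**Working it through.** **Inputs**

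- 225 per arm, 450 in total, 25% attrition (Sample size). Attrition is not given by arm.
- The protocol gives no event rates. The ratio *k*, the risk in those lost divided by the risk in those assessed, is therefore an assumption, shown over a range.
- It is also assumed that nothing is learned about those lost. This is the worst case, because the planned tracing would recover some events.

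**The plan's own figure**

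Pilot means of 5.9 and 6.4 with SD 1.5 give 0.5/1.5 = 0.333 SD. For two means, a two-sided 5% test then needs 142 per arm for 80% power and 162 for 85%, which matches the protocol. Allowing for attrition, 162/0.75 = 216, and 225 × 0.75 = 168.75, so 225 per arm is adequate. The sample size is not in question. Only its 25% is carried forward.

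**People without an assessment**

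- 225 × 0.25 = 56.25, or about 56 per arm.
- 450 × 0.25 = 112.5, or 112 to 113 in total.

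This is an upper figure for safety data, because it requires the same people to miss both assessments.

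**Share of events missed, with equal loss in both arms**

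Share captured = 0.75/(0.75 + 0.25*k*); share missed = 1 minus that.

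| *k* (assumed) | Captured | Missed |
|---|---|---|
| 1 | 0.75/1.00 = 75% | 25% |
| 2 | 0.75/1.25 = 60% | 40% |
| 3 | 0.75/1.50 = 50% | 50% |

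**Effect on the ratio between arms**

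Suppose the true risk is equal in the two arms, so the true risk ratio is 1.00. With loss *f* in an arm, the captured share is (1 − *f*)/((1 − *f*) + *f k*). The observed ratio on all randomised is the intervention share divided by the control share.

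| Assumed pattern (intervention v control) | Calculation | Observed ratio |
|---|---|---|
| 25% v 25% lost, *k* = 1 in both | 0.75/0.75 | 1.00 |
| 25% v 25% lost, *k* = 2 in both | 0.60/0.60 | 1.00 |
| 30% v 20% lost, *k* = 1 in both | 0.70/0.80 | 0.875 (1.00 among those assessed) |
| 30% v 20% lost, *k* = 3 in both | (0.70/1.60)/(0.80/1.40) = 0.4375/0.5714 | 0.77 (0.88 among those assessed) |
| 25% v 25% lost, *k* = 3 v 1 | 0.50/0.75 | 0.67 |

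Equal loss with the same risk pattern lowers the counts and leaves the ratio alone. A shift in the ratio needs a difference between arms in loss or in the risk of those lost.

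**Do other sources fill the gap?**

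- The question on hospital admissions avoids the association condition, but it is asked of participants at follow-up, so it is lost for the same people. It covers neither deaths nor suicide attempts.
- The record extraction does not depend on attendance, but it does not list the three events.
- Clinic managers and home visits may bring an event to light. Their stated purpose is to reach the participant and obtain the assessment, and the protocol does not say that a death or admission learned this way is recorded.
- The suicide-risk procedure in Ethics is triggered by the ninth PHQ-9 item, so it too needs an assessment.

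**The case against.** The text promises assessment of all participants and names no informant. Since death is on the list, self-report alone cannot be meant. Tracing is persistent, and under System to deliver the messages even participants who block the messages stay in follow-up unless they withdraw consent. Someone missed at three months may be reached at five. The 25% is a sample-size allowance for missing outcome data and does not predict how many people will have unknown vital status. Adverse-event procedures may also be set out in a document not shown.

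Much of this stands. A reader might infer that events can be learned of only from a completed interview; the tracing steps make that too strong. A reader might also infer that every event is screened for association before it is counted. No such step is described, and hospital admissions are asked about without the condition. Nor is there ground for saying that those collecting the events know the allocation, since the follow-up assessors are blinded.

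What does not fall away is the rule as written. The qualifier is in the sentence, the two follow-up assessments are the only stated occasion, and the listed extraction omits these events. These points concern how data are collected, which is not normally left to a statistical analysis plan.

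**Conclusion.** The concern holds as one of likely undercounting. If the protocol is followed as written, unrelated deaths and suicide attempts need not be counted, and no stated source covers the three events in people who are never assessed. At 25% loss, about 25% of events would be missed if those lost have average risk and 40% if they have twice the risk. These figures rest on the assumed risk ratios, on the same people missing both assessments, and on tracing recovering nothing, so they are upper figures for each assumed ratio. They do not include any events left out because of the association wording.

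A reader might go further and conclude that the harms comparison is biased. The document does not support that. It describes no such comparison, uses the same schedule in both arms, blinds the assessors and gives no sign of differential loss. The ratios of 0.67 to 0.88 above show what could happen under assumed differences between arms; they are not predictions.

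The statement in Ethics that risk is minimal is a prospective judgement, and this point does not contradict it. The primary analysis is unaffected.

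**What to change.** Three changes to Data collection and management:

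1. Drop the association condition from the definition. Count every death, hospitalisation and suicide attempt in both arms, and record judged relatedness in a separate field.
2. Add these three events to the electronic record extraction already planned for all 450.
3. State that when clinic managers or home visits are used to trace an unreached participant, any of the three events learned of is recorded, with its source, even if no assessment follows.

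Reports of harms should then give, by arm, the number of participants with an assessment, with record data only, and with neither, so that completeness can be judged.

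The cost is a few extra extraction fields and a wording change, which under Oversight and monitoring goes to the Ethics Committee for approval. The extraction adds no burden for participants. The limitation is that primary care records may not hold every hospital event or death, so the changes would reduce the undercount without guaranteeing its removal.
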